### Recruitment and consent process

Three large dialysis organizations have agreed to collaborate to implement this initiative. We will have a champion role that may be filled by any nephrologist at the site interested and willing to be part of the project. We are working in collaboration with the administration of the collaborating dialysis organizations to recruit social workers or nurses to participate. The dialysis organizations set their own criteria for which centers will be eligible to participate based on organizational priorities (e.g., dialysis centers who have completed installation of EMR, dialysis centers in a certain region). The dialysis organization will contact their employees with information about the HIGHway project using standard internal communication strategies such as email lists. Alternatively, others who learn of the project via marketing efforts by the Coalition for Supportive Care of Kidney patients may individually choose to apply directly to the project and will be enrolled if space is available in the training cohort. Currently, HIGHway is in the recruitment stage.

Standard consent processes as approved by the IRB will be used to enroll in the project training, and patients who are approached to participate in an audio recorded interview. As approved by the IRB, the consent for the audio-recorded conversation involves obtaining verbal consent, with a waiver of documentation of consent for patients who agree to have an ACP conversation recorded. To obtain this consent, a member of the project team will set up a WebEx call with social worker/nurse and patient and will explain the project, answer questions, and obtain verbal consent to audio record the conversation and create a transcription from the audio record. Once both have consented to the recording, the project team member will begin the recording, but leave the WebEx session so that the patient will have privacy during their conversation. Processes for temporarily storing the recording, creating, and storing a transcript for analysis, have been approved by the IRB.

### Implementation timeline

This implementation study will enroll three cohorts of social workers and nurses beginning in early 2022. The cohorts will receive initial training over six weeks. Then each cohort will participate in a 9-month action period with ongoing coaching and mentoring in ACP conversations. Monthly calls to discuss additional topics along with implementation coaching will take place during the action period. Follow-up data collection will occur at the end of the action period and the project is scheduled to close May 31, 2023.

### Implementation outcomes

Our project will focus on implementation outcomes as well as selected patient and provider outcomes for intended project goals. Success will be determined by adoption and effective use of the ACP approach within in-center as well as home dialysis settings. Patient and provider outcomes will be measured by the number of ACP conversations held and documented; POLST completed; the quality and fidelity of ACP conversation to the HIGHway process as taught during education sessions; provider evaluation of education activities in terms of impact on knowledge and skills; content, relevance, and significance of ACP intervention for patients, and SKD App usage.

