Social Worker/Nurse Online Survey	• Evaluation of training sessions includes both pre and post evaluation questions for comparison • Provide social worker survey (on-line) to evaluate participation in program, extent to which have adopted into ongoing workflow, identify facilitators and barriers, and assess future sustainability

Nephrologist and other clinic staff members will also have an opportunity to engage in both asynchronous and synchronous training. Training will focus on the HIGHWay model with opportunities to build skill around discussing ACP, and the role of the social worker, and importance of care coordination and interdisciplinary teamwork. Example video demonstrations and role plays will be used.

A computer application, The Supportive Kidney Care application (SKC App) enables dialysis center clinicians along the steps of an optimal ACP process. The first app was based on the Renal Physician Association “Shared Decision Making” Guidelines and provided tools to help dialysis center teams to assess prognosis and disease trajectory, guide discussion, and document goals of care with ACP forms. The revision of the app now follows the HIGHway roadmap and allows a more patient-centered, flexible process to occur and be documented. The app is optional for teams to adopt. We will evaluate the extent to which the app was useful and adopted by teams.

We work with the dialysis center teams to understand how ACP can be made a seamless part of regular workflow so that it does not require large amounts of additional resources. The process of folding ACP into existing workflow is part of the training and support provided to the dialysis center teams.

Around month 3–5 of the 9-month activity period, the social worker or nurse will select one patient to have an ACP conversation with and record the conversation with patient's consent. The lead social work faculty member will then hold an individual mentoring session with the social worker/nurse to provide supportive feedback to refine their communication skills.

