### Data collection

There are several distinct study populations for this study, with procedures and instruments for evaluation specific to each: 1) social workers/nurses participating in the training and implementation of intervention, 2) patients who agree to provide feedback on the advance care planning service they receive, 3) patients who agree to have an ACP session recorded.

Data on the number of ACP conversations conducted and the number of advance directives completed and filed in charts will be collected directly from the app for those teams that use it. In the alternative, sites that do not use the app will submit a brief weekly report via email with the number of ACP activities conducted that week as well as any successes or barriers encountered.

Fidelity check of the intervention will be performed by auditing a selection of the audiotapes of conversations between social works/nurses and patients to assess completeness of these conversations, to assess how adherent the visit was to the ACP checklist.

The anonymous survey for patients who attended an ACP session is based on previously validated Quality of Communication Scale, and adaptation of Patient Enablement Instrument. The survey’s purposes are to assess satisfaction with the ACP session, including change in confidence to complete ACP steps and quality of communication. Qualitative interviews of a sample of patients within dialysis center will be conducted to assess content, relevance and significance of ACP discussions based on a previously developed interview guide.

The implementation outcomes will be assessed through a survey to the participating social workers/nurses at the completion of their 9 months of participation. The questionnaire is based on the Workshop Evaluation Form (WEVAL). The questionnaire has been piloted with several social workers and adapted to the HIGHway project. Our main collection sources will be the evaluation questionnaires completed by the social workers or nurses, contingent on patients who consent to participate.

When an ACP conversation takes place, social worker/nurse will provide patient with an informational flyer about the project and a postcard with survey link. A Survey link will connect patient to a brief survey via Qualtrics (an encrypted survey system) regarding the conversation. Completion of survey will signify consent. The survey is anonymous.

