We plan to enroll 60 social workers or nurses total over the several training cohorts. The turnover and dropout are expected to be about 17%, resulting in target of 50 social workers/nurses who complete entire 9 months of training. The rational is the training capacity of the project. We expect that approximately 1,600 patients will receive ACP service because we will target each social worker/nurse conducting one ACP conversation per week during the 9 months of training, beginning after the first month. The proportion of patients who will participate in the post implementation survey is unknown. The target is 25% participation rate.

Quantitative analysis will be primarily descriptive, with descriptive statistics with confidence intervals to characterize survey responses on various questions. For several of the knowledge gain questions asked before and after the social workers engage in training, chi-square and t-tests will be used to assess change. Qualitative analysis will be used for both inductively and deductively assessing themes and subthemes. Given the short 2-year time frame for this project, and the proposed provision of ACP services to both seriously ill as well as stable dialysis patients, we have not tried to measure the impact of these activities on our end-users in terms of healthcare utilization or specific health outcomes or choices. Instead, the success of our ACP intervention—and receipt of goal-concordant care as the gold standard— is inferred from the high-quality communication based on our intervention, as demonstrated by the fidelity check of audiotaped ACP conversations and by patient survey responses. Further, we will measure the success of this implementation project by documenting that all ACP-related activities and discussions have taken place, by assessing the quality and completeness of GOC discussions, by mail-in survey of patients and family participating in discussions, and by qualitative interviews with selected patients.

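### Adoption is assessed by a self-rating survey of workers who reach month 9; the plan's own weekly conversation target, which could measure it across all enrolled workers, is not linked to it

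*Protocol article*

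**What the plan says.** All places are in the protocol article, Methods/design.

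- *Implementation outcomes* sets the criterion, for both in-center and home dialysis: "Success will be determined by adoption and effective use of the ACP approach".
- *Data collection* names the instrument: "The implementation outcomes will be assessed through a survey to the participating social workers/nurses at the completion of their 9 months of participation". This survey is adapted from a workshop evaluation form (WEVAL), and the worker evaluation questionnaires are called the main source of data. Table 1, under *Intervention activities*, shows that the online worker survey covers "extent to which have adopted into ongoing workflow, identify facilitators and barriers, and assess future sustainability".
- Conversation counts appear under a different label: "Patient and provider outcomes will be measured by the number of ACP conversations held and documented". They come from the app for teams that use it. Elsewhere they come from a weekly email report, which Table 1 says the social worker or nurse answers.
- *Data collection* also gives a target per worker: "we will target each social worker/nurse conducting one ACP conversation per week", starting after the first month. The target is used to derive about 1,600 patients receiving ACP. The same section plans 60 enrolled workers, about 17% turnover and dropout, and 50 completers.
- The analysis is primarily descriptive. It mentions confidence intervals for survey responses and tests for the knowledge questions asked before and after training. Success is further to be measured by "documenting that all ACP-related activities and discussions have taken place", together with the quality of discussions, patient surveys and interviews.

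**The concern.** The project's stated goal is to make ACP a routine part of each center's workflow. Adoption is then a property of a worker or center over time, and a scale-up project needs to know how many of those who started took it up.

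The instrument chosen has two weaknesses for that purpose. It is a retrospective rating by volunteers whom the Discussion itself describes as probably more open to ACP than average staff, so a favourable lean is plausible. It is also given only at completion of nine months, so workers who leave, who are plausibly less likely to have adopted, are not described by it.

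The counts are recorded closer to the event and could include leavers up to the time they go. The plan does not connect them, or its weekly target, to adoption. The one figure set for them is an aggregate, and an aggregate cannot separate wide uptake from a few high-volume workers.

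**Working it through.** **Inputs, all from *Data collection*:** 60 enrolled; about 17% leaving; 50 completers; one conversation per worker per week; nine months, counting from after the first, so eight months; about 1,600 patients.

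**Step 1. Reproduce the plan's figures.**
- Completers: 60 x (1 - 0.17) = 49.8, about 50. Leavers: 60 - 50 = 10, and 10/60 = 16.7%.
- Conversations: 8 months x 4 weeks = 32 weeks, and 50 x 32 x 1 = 1,600. This reproduces exactly. Calendar months would give 8 x 52/12 = 34.7 weeks and 50 x 34.7 = about 1,733, so the plan evidently used four-week months.

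**Step 2. What a total of 1,600 says about individual workers.** Total = sum over workers of weekly rate x 32. The distributions below are assumed, and the last is deliberately extreme.

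| Assumed pattern among 50 completers | Total | Averaging at least 1 per week |
|---|---|---|
| 50 workers at 1.0 per week | 50 x 32 = 1,600 | 50/50 (100%) |
| 25 at 2.0 per week, 25 at none | 25 x 64 = 1,600 | 25/50 (50%) |
| 20 at 2.0 per week, 30 at one every 3 weeks | 20 x 64 + 30 x 10.67 = 1,280 + 320 = 1,600 | 20/50 (40%) |
| 10 at 5.0 per week, 40 at none | 10 x 160 = 1,600 | 10/50 (20%) |

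The same total is compatible with anything from 20% to 100% of completers at the target.

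**Step 3. What the denominator does.** Suppose 40 completers meet the target and none of the 10 leavers does (assumed). Among completers the proportion is 40/50 = 80%. Among all enrolled it is 40/60 = 67%. The difference is 13 percentage points.

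**Step 4. Whether a worker-level proportion would be informative at this size.** The Wilson 95% interval is [p + z²/(2n) ± z√(p(1-p)/n + z²/(4n²))] / (1 + z²/n), with z = 1.96.
- 40/60 = 67%: interval 54% to 77%.
- 40/50 = 80%: interval 67% to 89%.
- 25/50 = 50%: interval 37% to 63%.

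These intervals are wide, but they distinguish majority uptake from uptake by a small minority.

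**The case against.** The strongest reply is that the worker survey does ask each participant how far ACP has entered the workflow. That is an adoption item per worker, and it addresses the project goal more directly than a count does. A reader might infer that the plan has no per-worker measure of adoption. The documents do not support that; the limits are self-rating and restriction to those who reach month nine.

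A reader might also infer that success could be declared on reaching 1,600, or on any conversations at all. Neither follows. The 1,600 is a planning expectation and not a threshold. The article does not say that counts will be reported only as a total. The sentence on documenting activities refers to all of them, which is vague but is not met by any non-zero count. Nor does success rest on the survey and counts alone: the fidelity audit, patient survey and interviews address effective use, although they do not show how many workers adopted.

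Three further objections stand in part.
- Weekly counts by worker are explicit only where the app is not used. App data are described by team with no stated interval, and the weekly report refers to ACP activities, which may be broader than conversations. Since a team is described as a social worker or nurse at a center, worker-level counts are probably derivable, but this has to be confirmed.
- The weekly email is self-report too. Its advantage is that it is made at the time, not that it is objective.
- One conversation per week is an activity target, not a definition of adoption, and a worker averaging slightly less would fall below it. It is nevertheless the only worker-level benchmark the plan states.

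Finally, a full protocol or analysis plan, not shown, may define adoption and per-worker summaries. Their absence from an article is not the point here. The point is the measurement choice that the article does state.

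**Conclusion.** The point holds as a measurement weakness that is cheap to repair. Adoption, half of the stated success criterion, is assessed by a retrospective self-rating that does not describe about 10 of the 60 enrolled workers. The activity counts that could supplement it carry only an aggregate expectation, which is compatible with between 10 and 50 of 50 completers reaching the weekly target. In the illustration, moving from completers to all enrolled lowers the proportion from 80% to 67%.

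The size rests on assumed distributions across workers and on assuming that leavers do not meet the target; the documents give no data on either. A favourable lean in the survey is plausible but not quantified. Because the project is descriptive, this calls for an improvement to how adoption is reported and does not invalidate the design.

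**What to change.** Alongside the survey, report adoption from the app or weekly-report counts already collected:

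- the proportion of all enrolled workers who average at least one ACP conversation per week over the counted weeks, with a 95% confidence interval;
- a rule for leavers, stated in advance (for example, weeks after leaving counted as zero, with the average over weeks in the project as a sensitivity analysis);
- the median and spread of conversations per worker.

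Before fixing this, confirm that app data can be attributed to a worker or center by week, and that the weekly report separates conversations from other ACP activities. Keep the survey for perceived adoption, facilitators and barriers, and keep the 1,600 as a description of volume.

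The cost is a few sentences of analysis text and possibly a small clarification of the weekly report or the app export. The adoption figure may look less favourable than a self-rating or a total, and the weekly email counts will still be self-reported, although recorded at the time.

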### Data collection

There are several distinct study populations for this study, with procedures and instruments for evaluation specific to each: 1) social workers/nurses participating in the training and implementation of intervention, 2) patients who agree to provide feedback on the advance care planning service they receive, 3) patients who agree to have an ACP session recorded.

Data on the number of ACP conversations conducted and the number of advance directives completed and filed in charts will be collected directly from the app for those teams that use it. In the alternative, sites that do not use the app will submit a brief weekly report via email with the number of ACP activities conducted that week as well as any successes or barriers encountered.

Fidelity check of the intervention will be performed by auditing a selection of the audiotapes of conversations between social works/nurses and patients to assess completeness of these conversations, to assess how adherent the visit was to the ACP checklist.

The anonymous survey for patients who attended an ACP session is based on previously validated Quality of Communication Scale, and adaptation of Patient Enablement Instrument. The survey’s purposes are to assess satisfaction with the ACP session, including change in confidence to complete ACP steps and quality of communication. Qualitative interviews of a sample of patients within dialysis center will be conducted to assess content, relevance and significance of ACP discussions based on a previously developed interview guide.

The implementation outcomes will be assessed through a survey to the participating social workers/nurses at the completion of their 9 months of participation. The questionnaire is based on the Workshop Evaluation Form (WEVAL). The questionnaire has been piloted with several social workers and adapted to the HIGHway project. Our main collection sources will be the evaluation questionnaires completed by the social workers or nurses, contingent on patients who consent to participate.

When an ACP conversation takes place, social worker/nurse will provide patient with an informational flyer about the project and a postcard with survey link. A Survey link will connect patient to a brief survey via Qualtrics (an encrypted survey system) regarding the conversation. Completion of survey will signify consent. The survey is anonymous.

We plan to enroll 60 social workers or nurses total over the several training cohorts. The turnover and dropout are expected to be about 17%, resulting in target of 50 social workers/nurses who complete entire 9 months of training. The rational is the training capacity of the project. We expect that approximately 1,600 patients will receive ACP service because we will target each social worker/nurse conducting one ACP conversation per week during the 9 months of training, beginning after the first month. The proportion of patients who will participate in the post implementation survey is unknown. The target is 25% participation rate.

Quantitative analysis will be primarily descriptive, with descriptive statistics with confidence intervals to characterize survey responses on various questions. For several of the knowledge gain questions asked before and after the social workers engage in training, chi-square and t-tests will be used to assess change. Qualitative analysis will be used for both inductively and deductively assessing themes and subthemes. Given the short 2-year time frame for this project, and the proposed provision of ACP services to both seriously ill as well as stable dialysis patients, we have not tried to measure the impact of these activities on our end-users in terms of healthcare utilization or specific health outcomes or choices. Instead, the success of our ACP intervention—and receipt of goal-concordant care as the gold standard— is inferred from the high-quality communication based on our intervention, as demonstrated by the fidelity check of audiotaped ACP conversations and by patient survey responses. Further, we will measure the success of this implementation project by documenting that all ACP-related activities and discussions have taken place, by assessing the quality and completeness of GOC discussions, by mail-in survey of patients and family participating in discussions, and by qualitative interviews with selected patients.

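### The worker survey on workflow adoption, barriers and sustainability is timed at 9-month completion, which about 10 of 60 workers are not expected to reach

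*Protocol article*

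**What the plan says.** The Implementation outcomes section sets the criterion: "Success will be determined by adoption and effective use of the ACP approach within in-center as well as home dialysis settings". Table 1 (Intervention activities) gives the online worker survey the task of assessing the "extent to which have adopted into ongoing workflow, identify facilitators and barriers, and assess future sustainability". Data collection fixes when that information is gathered: "The implementation outcomes will be assessed through a survey to the participating social workers/nurses at the completion of their 9 months of participation". The Implementation timeline agrees, placing follow-up data collection at the end of the action period.

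On numbers, Data collection says "We plan to enroll 60 social workers or nurses total over the several training cohorts", and then "The turnover and dropout are expected to be about 17%, resulting in target of 50 social workers/nurses who complete entire 9 months of training".

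Two other statements in Data collection matter here. Conversation and advance directive counts "will be collected directly from the app for those teams that use it"; sites without the app send a weekly email with activity counts, successes and barriers. On the worker questionnaires, the article says: "Our main collection sources will be the evaluation questionnaires completed by the social workers or nurses, contingent on patients who consent to participate".

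**The concern.** The instrument that asks how far the approach has entered ordinary workflow, what stood in the way and whether it will last is administered at a point that the plan expects one worker in six not to reach. Workers who leave early may well be those for whom the approach fitted worst, and they may know most about barriers. If they are not asked, the survey results describe the workers who stayed, and the planned descriptive confidence intervals would not show that extra uncertainty. The Discussion already accepts that volunteers are likely to be early adopters. A completer-only survey would probably add a second selection in the same direction.

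The sentence on patient consent adds a separate difficulty. Taken literally, it makes a worker's own questionnaire depend on whether patients agree to take part. The same section treats workers and patients as distinct populations with their own instruments.

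**Working it through.** **Inputs from the article (Data collection):** 60 workers enrolled; about 17% turnover and dropout; 50 completers; about 1,600 patients, at one conversation per worker per week over the 9 months, starting after the first month.

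**Reproducing the plan's figures**
- Completers: 60 × (1 − 0.17) = 49.8, which agrees with the stated 50. Expected leavers: 60 − 50 = 10, and 10/60 = 16.7%.
- Patients: 50 workers × 8 months × 4 weeks = 1,600, which agrees with the stated figure. With 60 workers it would be 60 × 8 × 4 = 1,920. The forecast therefore appears to rest on completers. (At 52/12 weeks per month, 50 workers give 1,733, so the match depends on 4-week months.)

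**Illustrating the effect on an adoption proportion**

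The article gives no adoption rate and no yes/no definition of adoption. The number of adopters among completers, x, is therefore an assumption, and a range is shown.
- Completer figure: x/50
- All enrolled, no leaver adopted: x/60
- All enrolled, every leaver adopted: (x + 10)/60

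| x | Completers | No leaver adopted | All leavers adopted | Completer figure minus lower bound |
|---|---|---|---|---|
| 25 | 50% | 41.7% | 58.3% | 8.3 points |
| 30 | 60% | 50.0% | 66.7% | 10.0 points |
| 35 | 70% | 58.3% | 75.0% | 11.7 points |
| 40 | 80% | 66.7% | 83.3% | 13.3 points |
| 45 | 90% | 75.0% | 91.7% | 15.0 points |
| 50 | 100% | 83.3% | 100% | 16.7 points |

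For x = 40, the Wilson 95% interval is 67.0% to 88.8% for 40/50, and 54.1% to 77.3% for 40/60.

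The lower bound is always 50/60 of the completer figure, a relative fall of one sixth. The two bounds are always 10/60 = 16.7 points apart. The completer figure is unbiased only if leavers adopt at the same rate as completers. With x = 40 that means 8 of the 10 leavers, since (40 + 8)/60 = 80%. With fewer than 8 it overstates; with 9 or 10 it understates, by at most 3.3 points.

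**What the other sources cover**

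| Information | Described source | Covers a leaver? |
|---|---|---|
| Conversation counts | App, or weekly email | Yes, until exit |
| Barriers, non-app sites | Weekly email | Yes, until exit |
| Barriers, app sites | Worker survey | Not by the stated timing |
| Extent of workflow adoption, sustainability | Worker survey | Not by the stated timing |

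**The consent sentence**

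Data collection opens by separating workers from two patient groups, with procedures specific to each. The patient survey is anonymous and completing it is the consent, so no link from a consenting survey respondent back to a worker is described. The sentence does not fit either statement.

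**The case against.** The strongest reply is that the worker survey is not the only measure of success. Activity data accrue throughout the action period. The article also says that success is measured by documented activities, the quality and completeness of discussions, patient and family surveys, and interviews. A reader might infer from the survey's timing that leavers disappear from the adoption result altogether. The documents do not support that: a worker who leaves in month 5 has already contributed conversation counts and, at a site without the app, barrier reports. The gap is confined to the survey items.

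Second, a reader might treat leavers as the non-adopters. The article speaks of turnover as well as dropout, does not split the 17%, and does not link either to adoption. A change of job is not evidence of non-adoption. The direction of bias is therefore probable, not established, and counting every leaver as a non-adopter is a worst case.

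Third, the article states no adoption endpoint, threshold or denominator, and the analysis is mainly descriptive. The handling of leavers may be set out in a full protocol or analysis plan that is not shown, and nothing in the text bars contact at exit. This stands as a limit on confidence. It does not remove the point, which rests on the timing the article states and not on what it omits.

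Fourth, the consent sentence could be read as a second selection of workers by success. It is more plausibly a clumsy joining of the worker and patient sources. It needs correcting, but it does not show that the worker sample is restricted.

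**Conclusion.** The point holds in a limited form. As written, the survey-based results on workflow adoption, barriers and sustainability would describe the expected 50 completers and not the 60 enrolled, and would probably lean toward success. Activity counts still cover leavers until exit. In the illustration, 80% among completers corresponds to 67% to 83% over all enrolled. For completer rates of 50% to 100%, the completer figure exceeds the lower bound by 8 to 17 points.

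This rests on three assumptions: that the 17% loss occurs as forecast, that adoption is summarised as a proportion, and that leavers are not surveyed at exit. The adoption rates are illustrative and are not figures from the plan.

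**What to change.** 1. Send the existing online worker survey at exit to every worker who leaves early, and ask the reason for leaving. The article describes recruitment as still open, so this can be done prospectively; barrier information from workers already gone may be hard to recover.
2. Report adoption and conversation activity with all enrolled workers as the denominator, alongside the completer figure and the number who left, with reasons.
3. Where exit data are missing, show two sensitivity bounds: no such leaver adopted, and all of them adopted. Neither should be the headline rule.
4. Correct the Data collection sentence so that worker questionnaires do not depend on patient consent, and state the patient sources and their consent separately.

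The cost is about 10 additional online surveys with the existing instrument, some changes of wording, and an adoption figure that may be less favourable.
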